## Abstract

**Background:**

Rheumatoid arthritis (RA) is known as a chronic systemic autoimmune disorder that primarily targets synovial joints, and may cause pain and functional limitations. Studies show diet can have beneficial effects on symptoms and oxidative stress of this disease. Intermittent fasting (IF) is a dietary approach with cycles of fasting and intake. The current study aims to investigate the effect of IF on quality of life, clinical symptoms, inflammation, and oxidative stress in overweight and obese postmenopausal women with RA.

**Methods:**

The current study is a randomized clinical trial, in which 44 patients with mild to moderate severity of RA will be randomly allocated to receive either IF (*n* = 22) or the usual diet (*n* = 22) for 8 weeks. Anthropometric measures and biochemical indicators including serum concentrations of erythrocyte sedimentation rate (ESR), c-reactive protein (CRP), and total oxidant and antioxidant capacity (TOC and TAC) will be assessed at the baseline and end of the study. Also, disease severity will be assessed by Disease Activity Score-28 (DAS-28) and clinical disease activity index (CDAI), and disability index will be assessed by Health Assessment Questionnaire-Disability Index (HAQ-DI) questionnaire.

**Discussion:**

Studies show fasting has beneficial effects on inflammatory markers and results in an improvement in the health of different populations. Literature review shows it seems there is no study in this field to evaluate the effects of IF on RA patients, and they are limited to other types of fasting. However, studies show IF can have many positive effects on chronic and autoimmune diseases. Therefore, IF may have positive effects on these patients.

**Trial registration:**

IRCT20230217057441N1. Registered on 14 February 2023. https://en.irct.ir/user/trial/68669.

**Supplementary Information:**

The online version contains supplementary material available at 10.1186/s13063-024-07977-2.

## Background

Rheumatoid arthritis (RA) is a chronic and systemic autoimmune disorder that primarily affects the synovial joints. This condition can cause pain, swelling, and stiffness, leading to a decrease in mobility and quality of life, and may cause pain and functional limitations [1]. RA is a widespread inflammatory arthritis that is one of the leading causes of disability and mortality around the world [2]. It can cause many symptoms like pain, dysfunction, fatigue, and depression, which may reduce the patient’s quality of life [3], and result in a promotion in the risk of cardiovascular diseases and a decrease in life expectancy [4]. The prevalence of this disease in the world is estimated at 0.5 to 1%, which has a large variation among different populations [5]. The prevalence of RA in Iran in 2016 was reported as 0.37% [6].

The pathophysiological mechanisms of RA have not been fully understood [7]. Studies suggest that RA is related to oxidative stress, a state where the supply of reactive oxygen species increases with time and results in increased production, decreased antioxidant defense, or a combination of both mechanisms and impaired redox signaling and molecular damage control [8, 9].

Studies have stated that in middle age, lifestyle, including nutrition, and physical activity play a role in the prevention and improvement of several health problems [10–13]. Evidence shows the effects of diet and nutrients on the progress of RA [14], and the role of them as a potential tool for preventing and managing disease [15]. It is also suggested eating habits can increase the risk of disease or be a protective factor against that [16]. In recent studies, dietary interventions show significant improvements in RA patients [17, 18]. For instance, a systematic review and meta-analysis demonstrate significant improvements in the anti-inflammatory diet in the pain score of RA patients compared to the control group [19]. Also, another review showed significant beneficial long-term impacts of fasting followed by a vegetarian diet on RA patients [20].

Intermittent fasting (IF) diets have recently become popular for improvement in many chronic diseases [21]. IF is one of the types of fasting diet suggested by experts and various studies because the potential benefits of weight control, cardiovascular health, and oxidative stress reduction make it an attractive option [22]. This type of fasting refers to not consuming food or restricting its consumption in a certain period, for example, 16 h a day [23]. It seems IF can have positive effects on improving the autoimmunity in several autoimmune diseases [24, 25]. Likewise, with hormone secretion and oxidatively related gene expression, IF can protect against oxidative stress and has immunomodulatory effects [26].

Due to the pathophysiology of RA, and the autoimmune feature of this disorder, it seems IF may have beneficial effects on RA patients. Literature review showed most of the studies conducted in the field of fasting and RA have investigated total or subtotal fasting [27–30], or calorie restriction [31, 32]. To the best of our knowledge, there is no published study about the effects of IF in these patients around the world. Therefore, according to the limitations of complete fasting in the form of no food intake or restriction of calorie intake, and mentioning that this study is the first study that investigates the effects of IF in these patients, the present study will examine the effects of IF in postmenopausal, overweight, and obese women with RA in a randomized control clinical trial and parallel group manner.

## Methods

### Study design and participants

In this randomized, controlled, parallel-group superiority trial, we compare the effects of the IF diet to the usual diet on clinical symptoms, inflammation, and oxidative stress in overweight and obese postmenopausal women who suffer from RA with the diagnosis of a rheumatologist and by the criteria of the American College of Rheumatology (ACR) over 8 weeks, with a 1:1 allocation ratio, in 2023–2024. This study will be conducted on eligible patients who will be referred to the rheumatology clinics of the Tehran University of Medical Sciences. Participants will be randomly allocated into a control group with the usual diet, and an intervention group with the IF diet. The protocol of this study was approved by the Ethics Committee of Tehran University of Medical Sciences (IR.TUMS.IKHC.REC.1401.376) and was registered at the Iranian Registry of Clinical Trials (IRCT20230217057441N1). After explaining the objectives of the study and the method of its implementation, documented informed assent is obtained from the attendees (Fig. 1).

**Fig. 1 Fig1:**
[figure not shown]
Standard Protocol Items: Recommendations for Interventional Trials (SPIRIT) chart of the enrollments and assessments during randomized controlled trials

Inclusion criteria are menopause women with a body mass index between 25 and 35 kg/m^2^, age range between 50 and 70 years, diagnosed with RA by a specialist for more than 6 months, have moderate to low RA disease activity (i.e., disease activity score <5.1), following a stable drug regimen for 3 months before the intervention, not receiving non-steroidal anti-inflammatory drugs (NSAIDs), and more than 7.5 mg of corticosteroids, and willingness to cooperate. Exclusion criteria are consumption of alcoholic beverages, suffering from other autoimmune diseases, kidney diseases, pancreatitis, gallstones, cancer, pregnancy, and breastfeeding, following a special diet in the last 3 months, changing the drug regimen from 3 months before the intervention. Figure 2 demonstrates the flow diagram of the project.

**Fig. 2 Fig2:**
[figure not shown]
Diagram of the study design

### Randomization

Participants will be randomized using stratified permuted blocks. A block size of 4 will be used, and stratification factors are the participant’s BMI (between 25 and 30 and 30 and 35 kg/m^2^) and whether they are receiving biological or non-biological drugs. People will be allocated to one of the two groups of intervention and placebo. Random allocation will be based on a random number list; the letters A and B will be assigned to an equal number of random number list. In this study, patients, doctors, and researchers are not blinded.

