#### Secondary outcomes

Secondary outcomes are the changes in erythrocyte sedimentation rate (ESR), C-reactive protein (CRP), disease activity score in 28 joints (DAS-28), Visual Analogue Scale pain intensity (VAS-pain), level of total oxidant and antioxidant capacity (TOC and TAC), oxidative stress index (OSI), tender joint count (TJC), swollen joint count (SJC), tender-swollen joint count difference (TSJD), morning stiffness count (MS), patient global assessment of disease activity (PGA), global assessment of disease activity (EGA), and clinical disease activity index (CDAI) from baseline values.

We will evaluate both primary and secondary outcomes two times, first after the run-in period, at the beginning of the intervention, and second, 8 weeks later.

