### Run-in period

Before starting the intervention, the selected people first will be entered into a 2-week run-in period to collect enough information about their food habits and intake. Then, by using a general information questionnaire about age, gender, education level, history of diseases and hospitalization, surgery, and history of taking drugs, supplements will be taken from all people. During this period, patients will complete a 24-h food record for 3 days including two working days and one day off per week, and questions will be asked about their eating habits. Before the intervention, anthropometric measures such as height, weight, waist circumference, and body composition, as well as biochemical evaluations including TOC, TAC, CRP, and ESR, will be measured and questionnaires related to the pain and inflammation will be collected. At the end of the run-in period and before the commencement of the intervention, people will be divided into blocks based on their BMI and medications received.

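### A single fixed block size of 4 in a fully open trial makes about 30% of allocations deducible, and the protocol does not settle whether baseline HAQ is taken before the arm is known

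*Protocol article*

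**What the plan says.** **Allocation.** The Randomization section of the protocol article says "Participants will be randomized using stratified permuted blocks" and "A block size of 4 will be used". The strata are BMI (25 to 30 and 30 to 35) and "whether they are receiving biological or non-biological drugs", which gives 2 × 2 = 4 strata. The allocation source is described as follows: "Random allocation will be based on a random number list; the letters A and B will be assigned to an equal number of random number". Study design and participants adds "with a 1:1 allocation ratio", so each block holds two patients per arm. On blinding, the Randomization section says "In this study, patients, doctors, and researchers are not blinded".

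**Baseline timing.** Secondary outcomes says "We will evaluate both primary and secondary outcomes two times, first after the run-in period, at the beginning of the intervention", with the second evaluation 8 weeks later. Run-in period first describes the measurements and the pain and inflammation questionnaires taken before the intervention. It then says "At the end of the run-in period and before the commencement of the intervention, people will be divided into blocks" according to BMI and medication. HAQ is not named there. Primary outcomes defines the primary endpoint as the change in HAQ from baseline.

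**The concern.** **Predictability.** With a fixed, known block size and visible past assignments, anyone who follows a stratum knows the remaining arm once one arm has filled its two places. Past assignments are visible here. Under Measuring the adherence to the diet, the researcher telephones every participant weekly and checks fasting in the intervention arm. Under Oversight and monitoring, one coordinator arranges visits and collects consent forms and also sits on the steering committee and the data management team. There is room to act on a prediction: willingness to cooperate is an inclusion criterion that needs judgement, and allocation comes only after a 2-week run-in. Who proceeds, and when, could follow the expected arm. That is selection bias, which randomisation is meant to prevent.

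**Baseline HAQ.** HAQ is self-reported and measured only twice. If a patient answers the baseline questionnaire already knowing her arm, any effect of that knowledge on her answers goes straight into the primary change score.

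**Working it through.** The protocol gives no figure for predictability, so there is none to reproduce.

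**Inputs.** Block size 4, four strata, no blinding (Randomization); 1:1 ratio (Study design and participants); 44 patients (Study sample size calculation). Assumption: the person guessing knows all earlier assignments, and their order, in the stratum.

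**Step 1: complete blocks.** The six equally likely sequences are AABB, BBAA, ABAB, BABA, ABBA and BAAB. An allocation is certain once one arm has its two places.
- AABB and BBAA: positions 3 and 4 are certain (2 each).
- The other four: only position 4 is certain (1 each).
- Mean = (2×2 + 4×1)/6 = 8/6 = 1.333 per block; 1.333/4 = **33.3%**.
- Best guess (choose the arm that is behind, toss a coin if level), by position: 0.5 + 2/3 + 2/3 + 1 = 2.833; 2.833/4 = **70.8%**, against 50% by chance.
- If all 44 patients fell in complete blocks: 44 × 0.333 = 14.7 certain.

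**Step 2: four strata with incomplete last blocks.** The mean stratum size is 44/4 = 11. Take a leftover of 0, 1, 2 or 3 patients as about equally likely, so 1.5 on average.
- Complete blocks per stratum: (11 − 1.5)/4 = 2.375.
- Certain allocations: 2.375 × 1.333 = 3.167. A leftover of 3 adds 1/3 with probability 1/4, that is 0.083. The sum is 3.25 per stratum.
- Four strata: 4 × 3.25 = **13.0 of 44 = 29.5%**.
- Best guess: 2.375 × 2.833 = 6.729, plus the leftover mean (0 + 0.5 + 1.167 + 1.833)/4 = 0.875. The sum is 7.604; 7.604/11 = **69.1%**.

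Simulation with random stratum sizes (40,000 runs) gives 13.0 certain allocations, with a 95% range of 10 to 16. The result is almost the same for equal and unequal strata.

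**Step 3: blocks of 4 and 6 in random order.** In this simulation the guesser knows the possible sizes but not which one was drawn, and updates after each assignment.

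| Four strata, 44 patients | Certain | Best guess right |
|---|---|---|
| Fixed 4 | 29.5% (13.0) | 69% |
| Random 4 and 6 | about 6% (0.06 × 44 = 2.6) | about 67% |

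Varied blocks remove most of the certainty but little of the guessing advantage.

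**Step 4: order of baseline HAQ and allocation.**
- Secondary outcomes puts the first evaluation after the run-in, at the start of the intervention.
- Run-in period puts the division into blocks at the end of the run-in, before the intervention. Taken literally with the first statement, HAQ follows allocation.
- Run-in period also describes the pre-intervention measures ahead of that division. Taken as a sequence, baseline precedes allocation.
- Being divided into blocks by BMI and medication may describe stratification only. Neither section says when the patient learns her arm.

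The text supports both orders and fixes neither.

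**The case against.** **The magnitude can be overstated.** A reader might apply one third to all 44 patients and report about 15. That assumes every block is complete; with four strata about 13 is the expected number. Someone must also track four strata separately. Because consent and a 2-week run-in come first, steering at recruitment means forecasting the block position two weeks ahead, and otherwise it must happen at the end of the run-in. All of this stands. It narrows the risk without removing it.

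**Concealment may be described elsewhere.** Who holds the list and how it is released is detail that an article may leave to the full protocol, so its absence is not a finding. Concealing the list would not cure the problem, however, since the end of a block can be deduced from arms already visible.

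**A reader might infer that baseline HAQ is taken after allocation.** That is one reading of two sections, and the protocol nowhere states it. The schedule chart and the flow diagram, which could settle the order, are not shown in the text at hand. Only the lack of a clear order in the text can be claimed.

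**A reader might infer that an unblinded rheumatologist does the joint counts and the global assessment (EGA).** The protocol does not name the assessor of either; under RA diagnosis the rheumatologist is given the diagnosis only. Keeping the arm from that assessor would in any case not protect the primary outcome, which the patient reports. The Strengths and limitations section already concedes that subjective judgement may influence outcome evaluation.

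**The fix has limited reach.** Best-guess success barely falls, and recruitment was planned to end in December 2023, so a new list may reach few patients or none. Both points stand and are reflected in the fix.

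**Conclusion.** The concern holds in a limited form. A single fixed block size of 4 in a fully open trial makes one third of allocations certain in complete blocks. About 13 of 44 (30%; 95% range 10 to 16) are expected with four strata and incomplete last blocks. This rests on someone knowing earlier assignments and tracking them by stratum. It shows an opportunity for selection bias, not that bias occurred.

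The order of baseline HAQ and disclosure of the arm is unresolved between Secondary outcomes and Run-in period. Direct bias in the primary change score follows only if HAQ is answered after the arm is known, which the protocol does not establish. The change should be made, but nothing here by itself invalidates the trial.

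**What to change.** 1. **Block sizes.** For patients still to be randomised, use randomly varied block sizes (for example 4 and 6) and do not disclose them to those who enrol. The main gain is fewer certain allocations, from about 30% to about 6%.
2. **Order of steps.** Reconcile Secondary outcomes and Run-in period so that eligibility is confirmed and all baseline measures, HAQ first, are complete before the arm is revealed. This protects the primary outcome most directly and also limits what anyone can do with a correct guess.
3. **Assessment.** Where whoever already does the joint counts and EGA can be kept unaware of the arm, do so, and code the laboratory samples. This helps CDAI, DAS-28 and the laboratory outcomes, but not HAQ.
4. **If recruitment is complete.** Report the fixed block size and the actual order of baseline HAQ and allocation as limitations.

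**Cost.** A new list for the remaining patients, a fixed order within the baseline visit, and sample coding. The downside is a slightly larger possible imbalance within strata.

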## Study hypothesis

We hypothesized that the IF diet has a beneficial effect on quality of life, clinical symptoms, inflammation, and oxidative stress in postmenopausal, overweight, and obese women with RA.

### Outcome measures

#### Primary outcomes

In the current study, the primary outcome is the changes in health assessment quality (HAQ) score from baseline values.

#### Secondary outcomes

Secondary outcomes are the changes in erythrocyte sedimentation rate (ESR), C-reactive protein (CRP), disease activity score in 28 joints (DAS-28), Visual Analogue Scale pain intensity (VAS-pain), level of total oxidant and antioxidant capacity (TOC and TAC), oxidative stress index (OSI), tender joint count (TJC), swollen joint count (SJC), tender-swollen joint count difference (TSJD), morning stiffness count (MS), patient global assessment of disease activity (PGA), global assessment of disease activity (EGA), and clinical disease activity index (CDAI) from baseline values.

We will evaluate both primary and secondary outcomes two times, first after the run-in period, at the beginning of the intervention, and second, 8 weeks later.

### Run-in period

Before starting the intervention, the selected people first will be entered into a 2-week run-in period to collect enough information about their food habits and intake. Then, by using a general information questionnaire about age, gender, education level, history of diseases and hospitalization, surgery, and history of taking drugs, supplements will be taken from all people. During this period, patients will complete a 24-h food record for 3 days including two working days and one day off per week, and questions will be asked about their eating habits. Before the intervention, anthropometric measures such as height, weight, waist circumference, and body composition, as well as biochemical evaluations including TOC, TAC, CRP, and ESR, will be measured and questionnaires related to the pain and inflammation will be collected. At the end of the run-in period and before the commencement of the intervention, people will be divided into blocks based on their BMI and medications received.

### Intervention

The participants in the intervention group follow the IF diet (16:8) in which they are only allowed to receive water and non-energy drinks, tea, coffee, and sugar-free gums for 16 h and 8 h in free consumption mode; they will receive food along with healthy diet recommendations for eight weeks; and the control group will receive their usual diet, along with healthy diet recommendations. To evaluate the level of adherence to the patient’s diet during the intervention, four 24-h food records (including two working days and one day off) will be collected from the patients once every 4 weeks and the physical activity will be checked every 4 weeks using the physical activity registration form and the patients will be asked to record these four physical activities in a way that includes at least two working days and two weekend days. All subjects will be asked in their physical activity not to have any change and medication and its dosage during the study compared to the beginning of the study. If there is a change in the type and dosage of the medicine received, participants will be excluded from the study. For better compliance of participants with the intervention, phone calls will be made with participants every week during the study and possible problems related to compliance with the IF diet will be investigated and necessary guidance will be given. At the end of the intervention, all the evaluations performed at the beginning of the study, including anthropometric indicators, body composition, biochemical evaluations, and questionnaires related to the amount of pain and inflammation in patients with RA, will be evaluated. If adherence to the prescribed diet is < 70% (failure to attend more than 3 phone sessions in a row, or 3 times of non-observance of the fasting diet per week for more than 2 consecutive weeks, changing the type and dosage of drugs received during the study), using new drugs and supplements and changing the dosage of the drugs being used and worsening the disease by the patients, they will be excluded from the study. An announcement to participate in this study will be printed and distributed.

### Measuring the adherence to the diet

To encourage adaptation to the IF diet and to have a healthy food intake, during the intervention, all subjects will have weekly and monthly meetings with a nutritionist so that while the intervention group follows the IF diet, all the studied subjects will use the strategies for healthy food intake. In addition, all patients will be given written and verbal instructions for healthy diet recommendations, and as mentioned, there will be no disparity between the participants in the intervention and control groups. Monitoring of the fasting diet is done through the daily interaction of the researcher and the participant in the project (for example, through telephone conversations, taking a 3-day food record). The researcher will hold weekly telephone meetings with all participants to answer questions and check compatibility with the fasting diet in the intervention group. To measure the compliance of the people in the intervention group, if they do not attend more than two phone sessions in a row, or if they do not follow the fasting diet three times a week for more than two consecutive weeks, they are considered non-compliant. In addition, the researcher provides instructions on keeping accurate records of portion sizes and food items to the participants [33].

